### Statistical analysis

As our design has two independent groups that acquire comparability by randomization, we can compare variables not only within each group, but also between groups.

The primary outcome of our research will be to compare the blinding rates of the placebo acupuncture devices studied within and between groups. We will also conduct several exploratory secondary outcome analyses. Expectation for acupuncture (measured by AEQ) [6], previous acupuncture experiences, and age will be considered as covariates. We will analyze physiological data in three tonic responses (before, during, and after acupuncture) and during phasic responses. We will not statistically compare the Bang’s BI [9]. Instead, we will calculate the point estimate and 95 % confidence interval of Bang’s BI.

For dichotomous variables (i.e., blinding rate), within group comparison will be performed using Cochran’s Q test for Group 1 (Sham ST, Real ST, and PHNT) and McNemar’s test for Group 2 (Sham, Real Park). We will not check the blinding of the No treatment session. Comparisons of blinding rates between group devices (Sham ST vs Sham Park or PHNT vs Sham Park) will be performed using the chi-square test, and comparisons within group devices (PHNT vs Sham ST) will be performed using McNemar’s test. For continuous variables (i.e., the MASS index, De-qi sensation, physiological data such as HR, HRV, and SCR), within group comparisons will be performed using repeated measured ANOVA for Group 1 and paired *t*-test for Group 2. We will use the independent *t* test for comparisons between group.

When we analyze physiological data, we will use the both change ratio contrast to baseline and absolute value. Change ratio and absolute value of HR and SCR will be compared for three separate windows during the tonic responses (before vs during vs after acupuncture session). As absolute change value is very dependent on baseline value, it will be used as covariates.

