**Methods/Design:**

The proposed study is a single-center prospective random sequence participant- and assessor-blinded trial with two parallel arms. A total of 76 participants will be randomly assigned to Group 1 or Group 2 in a 1:1 ratio. Group 1 will consist of Sham Streitberger’s needle, Real Streitberger’s needle, and Phantom acupuncture session. Group 2 will consist of Park Sham device with real needle, Park Sham device with sham needle, and no treatment session. Participants will have a total of three acupuncture sessions in a day. The primary endpoint is blinding test questionnaire 1. Secondary endpoints are the Bang’s blinding index, the Massachusetts General Hospital Acupuncture Sensation Scale index, and physiological data including heart rate, heart rate variability, and skin conductance response.

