## Methods/Design

### Objectives

The objectives of this trial are to evaluate the validity of different types of placebo acupuncture devices and determine their suitability for use as placebos in clinical trials.

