### Sample size calculation

This will be a kind of mechanism study, so we did not follow the general method to calculate sample size. It is known that a sample size of 12 or more is adequate for a pilot study [15, 16]. We concluded that we will have sufficient analytical power if our sample size is greater than 12. We decided that we need to enroll at least 30 participants in our pilot study for each session assuming a drop-out rate of approximately 20 %. We calculated a sample size of 37.5 and rounded to this to 38 resulting in a total sample size of 76 participants.

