The PSD developed by Park et al. was validated in two randomized controlled trials (RCTs) in acute stroke patients and acupuncture-naïve, healthy volunteers [18]. The study was designed to evaluate if PSD was indistinguishable from a real acupuncture needle and if PSD induced de-qi. They found that PSD was indistinguishable and inactive (in terms of de-qi), thus it is a valid placebo control for acupuncture research.

However, these previous two devices touch the skin and thus induce a physiological effect. To overcome this limitation, Lee et al. developed a phantom acupuncture technique that imitates the acupuncture treatment ritual without any tactile stimulation [5]. They showed the credibility of phantom acupuncture without somatosensory components of real acupuncture in healthy participants.

In summary, three types of placebo acupunctures were all evaluated to blinded participants using validation tests. In this study, by measuring blinding, de-qi sensation, and various physiological parameters such as HR, HRV, and SCR, we will investigate if placebo acupuncture techniques are indistinguishable from real acupuncture and physiologically inert.

This trial will evaluate the relevance of using placebo acupuncture devices in control groups using a validation test of various placebo acupuncture devices that have been used in acupuncture research.

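### The aim is to show that placebos cannot be told from real needling, but BTQ 1 blinding rates are only tested for a difference, with no interval, and Group 1 has no pairwise contrast with the real needle

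*Protocol article*

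**What the plan says.** The Background makes being indistinguishable from real acupuncture, to a blinded participant, the first of two conditions for a placebo. The Objectives section says the trial will "determine their suitability for use as placebos in clinical trials". The Discussion says "we will investigate if placebo acupuncture techniques are indistinguishable from real acupuncture and physiologically inert".

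The Statistical analysis section gives the primary outcome as a comparison of the placebo devices' blinding rates, within and between groups. It names these tests:

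- Group 1: Cochran's Q across Sham ST, Real ST and PHNT.
- Group 2: McNemar's test of Sham Park against Real Park.
- Between groups: chi-square for Sham ST against Sham Park, and for PHNT against Sham Park.
- Within Group 1, pairwise: "comparisons within group devices (PHNT vs Sham ST) will be performed using" McNemar's test.

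The only interval planned is a 95% confidence interval for Bang's blinding index, a secondary endpoint that will not be compared statistically.

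On size, the Sample size calculation section says "we did not follow the general method to calculate sample size" and "we need to enroll at least 30 participants in our pilot study for each session". It states no power, expected blinding rate, difference or margin.

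**The concern.** The aim is a claim of no difference, and a difference test that fails to reject does not establish one. The smaller the sample, the easier it is not to reject, so a device that is clearly less credible than the real needle can produce an unremarkable p-value. Without an interval for the difference, a reader of the results cannot see how large a deficit remains possible.

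Group 1 has a second problem. Cochran's Q tests whether three rates are equal. If it is significant, the next question is which placebo differs from Real ST, and the only follow-up pair named leaves Real ST out. Both between-group pairs are also placebo against placebo. Group 2 does have its direct sham-against-real test, so the same question is handled differently in the two groups.

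**Working it through.** **The plan's own figure.** At least 30 participants per session and about 20% drop-out: 30 / (1 − 0.20) = 37.5, rounded up to 38; 2 × 38 = 76. This reproduces the stated numbers. So 30 to 38 pairs per group are available.

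**Assumptions, since the article gives none.** Two-sided alpha 0.05; real-needle blinding rate 90–95%; placebo 10 to 20 points lower. McNemar is computed in the exact and the uncorrected chi-square forms, because the article does not say which applies. Within-person dependence is taken at two settings: independent responses, and fully nested responses (nobody is blinded by the placebo but not by the real needle).

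**Power for 95% against 80%.** McNemar's test uses only the discordant pairs.

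- Independent: P(blinded by real only) = 0.95 × 0.20 = 0.19; P(blinded by placebo only) = 0.80 × 0.05 = 0.04.
- Nested: 0.15 and 0.

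Summing over all discordant counts gives:

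| Pairs | Exact, independent | Exact, nested | Uncorrected, independent | Uncorrected, nested |
|---|---|---|---|---|
| 30 | 25% | 29% | 40% | 68% |
| 38 | 37% | 51% | 49% | 84% |

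The nested exact figure can be checked directly. Five discordant pairs all one way give p = 2 × 0.5⁵ = 0.0625, and six give 0.031, so rejection needs at least six. With 30 pairs and probability 0.15, the chance of six or more is 0.289. The uncorrected test needs only four (chi-square 4.0, p = 0.046), with chance 0.678.

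**Other differences, 30 pairs.** A 10-point drop (95% to 85%, or 90% to 80%): 7–10% exact, 17–35% uncorrected. A 20-point drop (95% to 75%, or 90% to 70%): 36–57% exact, 46–88% uncorrected. With 38 pairs the exact test still has only 14–17% for a 10-point drop.

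**Cochran's Q, n = 30** (simulated, 20,000 runs, independent responses). Both placebos 10 points below real: 16–20%. Both 20 points below (90/70/70): 47%. One of the two 20 points below: 54–68%.

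**What a null result leaves open.** If the true rates are equal and responses independent, the 95% half-width for a paired difference is about 1.96 × √(2p(1 − p)/n):

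| Common rate p | n = 30 | n = 38 |
|---|---|---|
| 95% | 11 points | 10 points |
| 90% | 15 points | 13 points |
| 80% | 20 points | 18 points |

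As an example, suppose 5 of 30 participants are discordant, all against the placebo. The difference is 5/30 = 16.7 points with standard error √(5 − 25/30)/30 = 0.068, so the Wald interval is about 3 to 30 points. The exact test gives p = 0.0625, which is not significant.

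**The case against.** Four points can be made for the plan.

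*Real ST is in the analysis.* Cochran's Q includes it, so a reader who infers that Group 1 never compares a placebo with the real needle goes too far. What is missing is a separate contrast for each placebo. Follow-up pairs after an omnibus test could be left to an analysis plan, but this section does list its pairs, and the Group 1 pair it lists is placebo against placebo.

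*No passage says a non-significant p-value will be read as validity.* This is correct. A reader may infer it from the stated aim combined with difference tests alone, but the article gives no reading rule of either kind. Bang's index with its interval is an estimation route as well. It softens the problem without curing it, because it is secondary and is not a paired difference in BTQ 1 rates.

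*The placebo-against-placebo tests match the stated primary outcome.* They do, and they should stay.

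*The power figures are illustrative.* They rest on assumed rates, alpha and correlation. A threshold of six discordant pairs (20 points with 30 pairs) holds only for the exact test; the uncorrected test can reject with four (about 13 points). It is also tempting to set a 20-point margin because the sample might support it. With 30 pairs, one-sided 0.025, equal rates and independent responses, power for that margin is about 94%, 73% or 49% at rates of 95%, 90% or 80%. Such a margin would be fitted to the sample size, and it would tolerate the 15-point deficit used as the example above. Nothing in the article supports it.

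**Conclusion.** The point holds in this form. The aim is a no-difference claim, the primary endpoint is analysed only by difference tests, no interval for a blinding-rate difference is planned, and no Group 1 placebo is contrasted separately with its real needle. With 30 to 38 pairs, non-significance is compatible with deficits of about 10 to 20 points. For a true 15-point deficit (95% against 80%), McNemar power lies between about 25% and 68% with 30 pairs and between about 37% and 84% with 38, depending on the test version and within-person dependence. The exact values depend on the assumptions listed; the direction is the same at every setting tried. The documents do not show that the sponsor intends to treat p > 0.05 as proof of validity, and the direct real-needle contrast is present in Group 2.

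**What to change.** In the Statistical analysis section:

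1. Add three paired differences in BTQ 1 blinding rate as named primary contrasts: Sham ST minus Real ST, PHNT minus Real ST, and Sham Park minus Real Park. Keep the planned placebo-against-placebo comparisons and Cochran's Q alongside them.
2. Report each with a 95% confidence interval suited to sparse paired data, such as a score-type interval. The Wald interval collapses to zero width when there are no discordant pairs.
3. State that any claim of indistinguishability rests on these intervals and that p > 0.05 alone does not support one.
4. If a margin is used, justify it by how much loss of credibility would matter, not by the available sample size, and fix it before results are seen. The article says recruitment is under way.

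This changes wording only and uses responses already being collected. The cost is that conclusions become more cautious and some devices may end up inconclusive.

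### Baseline and other covariates are announced, but most comparisons are given tests with no covariate term, and the change ratio is compared across windows against an undefined baseline

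*Protocol article*

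**What the plan says.** All of the following is in the protocol article.

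**Covariates (Statistical analysis).** Expectation (AEQ), "previous acupuncture experiences, and age will be considered as covariates". For physiology the wording is firmer: "As absolute change value is very dependent on baseline value, it will be used as covariates". The pronoun is loose, but the sensible reading is that the baseline value is the covariate.

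**Tests (same section).**
- Blinding, within group: "within group comparison will be performed using Cochran’s Q test for Group 1 (Sham ST, Real ST, and PHNT"), with McNemar's test for Group 2.
- Blinding, between groups and for phantom against sham Streitberger: comparisons between groups "will be performed using the chi-square test, and comparisons within group devices (PHNT vs Sham ST) will be performed using McNemar’s test".
- Continuous outcomes, within group: "within group comparisons will be performed using repeated measured ANOVA for Group 1", and the paired t-test for Group 2.
- Continuous outcomes, between groups: the independent t "test for comparisons between group".

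**Scale and windows (same section).** For physiological data, "we will use the both change ratio contrast to baseline and absolute value". Then: "Change ratio and absolute value of HR and SCR will be compared for three separate windows during the tonic responses", the windows being before, during and after needling.

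**Baseline.** The section does not define it. Procedures of each session describes a 5-minute resting recording before needling in every session. Phantom acupuncture and no treatment session says instead that the No treatment recordings serve as a baseline. Under Study flow, Group 1 never has a No treatment session.

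**The concern.** The section announces covariates and also fixes the tests, and for most comparisons the two cannot both be carried out. An analyst who follows the named tests drops the baseline adjustment that the section itself calls necessary. An analyst who follows the covariate sentence has to abandon the named tests, and would choose the replacement model with no rule to follow.

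The ratio raises a separate problem. A ratio to baseline carries no information in the window that defines the baseline. Comparing that window with the other two tests a constant against a noisy ratio whose mean lies above 1 even when nothing has changed. The comparison of HR and SCR across windows could then show a response that the needling did not cause, in a trial that asks whether placebo devices are physiologically inert.

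**Working it through.** **Step 1: which named procedures can take a covariate.**

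| Comparison | Named test | Covariate term |
|---|---|---|
| Blinding, Group 1 | Cochran's Q | none |
| Blinding, Group 2; phantom vs sham Streitberger | McNemar | none |
| Blinding, between groups | chi-square | none |
| Continuous, Group 1 | repeated-measures ANOVA | none as named; can be extended |
| Continuous, Group 2 | paired t | none |
| Continuous, between groups | independent t | none |

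Five of six procedures have no covariate term. The sixth can be extended to an ANCOVA for participant-level covariates such as age. In its classical form it does not take a baseline that changes from session to session. The article names no ANCOVA, regression, logistic or mixed model.

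**Step 2: the number of participants.** Sample size calculation asks for at least 30 per session with 20% drop-out: 30/(1 − 0.20) = 37.5, rounded to 38, and 2 × 38 = 76. This reproduces the stated total, so 30 evaluable per group is used below.

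**Step 3: the ratio, if baseline is the before window.** Let X0, X1 and X2 be the before, during and after values. The compared quantities are X0/X0 = 1 (variance zero), X1/X0 and X2/X0. The article gives no variances or correlations, so I assume lognormal values with equal means, between-person coefficient of variation CV, and correlation ρ on the log scale. With σ² = ln(1 + CV²) and no true change, the expected ratio is

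E(X1/X0) = exp{σ²(1 − ρ)}.

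At CV 0.8 and ρ 0.3: σ² = ln 1.64 = 0.495, and exp(0.495 × 0.7) = 1.414. At CV 0.12 and ρ 0.3: σ² = ln 1.0144 = 0.0143, and exp(0.0143 × 0.7) = 1.010.

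Simulated rejection rates of the three-window repeated-measures ANOVA on the ratio (n = 30, 5,000 runs per cell, nominal 5%, no true change):

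| CV | ρ = 0.3 | ρ = 0.5 | ρ = 0.7 | ρ = 0.9 |
|---|---|---|---|---|
| 0.12 | 6.0% | 5.7% | 5.7% | 5.2% |
| 0.3 | 11.1% | 8.6% | 7.3% | 5.7% |
| 0.6 | 22.0% | 17.4% | 12.9% | 7.3% |
| 0.8 | 28.4% | 24.2% | 17.1% | 9.6% |

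Simulation error in the largest cell is about ±1 percentage point, so a repeat run can give 29%. The same ANOVA on absolute values rejects 4% to 5% throughout. A Greenhouse–Geisser correction does not cure the ratio (still 23.9% in the largest cell), because the problem is mostly the shifted mean rather than unequal variances.

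If the sentence means instead that devices are compared within each window, the before-window ratio is 1 for every device and there is nothing to test.

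**Step 4: the ratio, if baseline is the No treatment session.** The ratio can then be formed within person in Group 2 and is not constant in the before window. It cannot be formed within person in Group 1.

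**Step 5: what the between-group t-test gives up.** With correlation r between baseline and outcome (assumed), adjusting for baseline leaves 1 − r² of the raw variance. Take the effect that has 80% power under the t-test with 30 per group, two-sided 5% (assumed): √(2/30) × (1.960 + 0.842) = 0.72 SD. Power after adjustment is Φ{2.80/√(1 − r²) − 1.96}.

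| r | Variance left | Power |
|---|---|---|
| 0.3 | 0.91 | 84% |
| 0.5 | 0.75 | 90% |
| 0.7 | 0.51 | 97.5% |

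These figures compare the adjusted analysis with the raw absolute value, not with the change ratio.

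**The case against.** The best defence is that the named tests are the unadjusted main comparisons, and that the covariates belong to exploratory models left to an analysis plan that is not shown. The sentence on expectation, experience and age directly follows the one announcing exploratory secondary analyses, and it says only that they will be considered. The Discussion describes exploratory work of that kind. For these three covariates the defence largely stands: they are not a firm promise. It does not cover the baseline covariate, which is stated as something that will be used, for the same outcomes that are assigned t-tests.

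A reader might go further than the article allows in four ways.
- *No named test can take covariates.* Group 1's repeated-measures ANOVA can be extended.
- *The ratio-by-window test is degenerate or cannot be run.* It runs. It is miscalibrated, by little at low CV and by a lot at high CV, and only if baseline is the before window.
- *The between-group comparisons are biased without adjustment.* Randomization keeps them valid; the loss is precision.
- *SCR baselines lie near zero, or the HRV measures are too skewed for t-tests.* The article gives no figures to support either, and transformations are ordinary analysis-plan detail.

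**Conclusion.** The concern holds in a limited form. The Statistical analysis section announces a baseline covariate for physiology beside tests that cannot use one, except in Group 1. It also leaves undefined the baseline on which the change ratio rests. Neither baseline found elsewhere in the article works as written: the before window makes one compared level constant, and the No treatment session does not exist for Group 1.

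On the first reading, the false-positive rate of the three-window ratio test runs from about 5% to 28% or 29%. It is close to nominal when values vary little between people or windows are highly correlated. For the between-group t-tests the loss is precision, from 9% of the variance at r = 0.3 to 49% at r = 0.7. The CVs, correlations and lognormal shape are assumptions; the article gives none.

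The consequences fall on secondary physiological outcomes. The unadjusted blinding comparisons, which are primary, remain valid; they are affected only if adjustment for expectation, experience and age was meant for them. This should be corrected, but it does not threaten the trial's main result.

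**What to change.** 1. Define baseline once, as each session's own before window, and reword the covariate sentence so that it is clearly the baseline value that is adjusted for. State separately what the No treatment recordings are used for.
2. Analyse the during and after windows by ANCOVA (between groups) or a linear mixed model (within groups, where baseline differs by session), with that baseline as covariate. This replaces the t-tests and the ratio-by-window test for the physiological outcomes.
3. If the change ratio is still reported, drop the before window as a compared level.
4. Where blinding is to be adjusted for expectation, experience and age, add a logistic model, penalised if blinding failures are few, as support for the unadjusted tests. Otherwise, withdraw the statement that these are covariates for blinding.

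The cost is wording and a little more analysis work. The before-window recordings and the AEQ are already in the planned data collection, and age is part of the demographic information. Experience is already named as a covariate. The sample size does not change.

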### Quality control

Before the study begins, we will conduct several simulations using our colleagues and volunteers to identify any problems with our study protocol. Practitioners will conduct acupuncture sessions according to the standard operating procedure (SOP) of our study. We will have researcher meetings regularly to discuss issues that may be raised by investigators and participants such as protocol revisions, serious adverse events, and participant recruitment.

### Safety and adverse event outcomes

When each session is completed, the assessor will ask if any AE occurred and it will be documented in the CRF. If any AEs occur, the type of AE, start/end date, severity, manner of report, course, outcome, causality with acupuncture treatment, and actions taken will be documented and appropriate treatment will be provided to the participants.

### Ethics approval and registration

This study has been approved by the Institutional Review Board of Kyung Hee University Korean Medicine Hospital (KOMCIRB-140923-HR-008). Written informed consent will be obtained from all participants. This study has been registered with the Clinical Research Information Service (CRIS), Republic of Korea, KCT0001347 (registered: January 15th, 2015).

